### Aim

3.1

This study aims to evaluate the effects of ISP for Chinese primiparous women in terms of improving the levels of *MSE*, social support, and satisfaction; and reducing their postpartum depression symptoms.

The study hypothesizes that compared with the control group at baseline, post‐test 1, and post‐test 2, women in the intervention group will report statistically significant:
Improved *MSE* and social support;Reduced postpartum depression symptoms; and.Great satisfaction with healthcare received after childbirth.

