#### Study setting and participants

3.2.2

The research will be carried out in the two university‐affiliated tertiary public hospitals in China, where the live births in each study hospital are over 2,000 babies per year. The inclusion criteria will be: first‐time mothers with healthy babies; aged 18 years or above; married; and able to response the questionnaires. Exclusion criteria will be: women or their children have severe physical and mental diseases.

Sample size will be estimated based on previous research with a medium to small effect size (Cohen, 1992). With a power of 0.80, an alpha set at 0.05, and an effect size of 0.35 for the primary outcome of PPD (EPDS scores), each group will be 90 women (Gao et al., 2012). We estimate a 30% attrition rate based on an attrition rate of 9%–29% in previous research (Gao et al., 2012). A minimum of 258 women (129 in each group) are required.

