#### Recruitment

3.2.3

Participants will be recruited when women are admitted in the obstetric wards of hospitals. The obstetric nurses will introduce the ISP to women who meet the inclusion criteria. Posters and leaflets about the program also will be strategically distributed in the obstetric wards to inform all women and their family members. Women who verbally agree to participants will be approached by the researchers to provide them with an information sheet and to answer their any questions about the research. In this approach, women were not asked to give consent as it was considered important to make sure that women had enough time (at least 1 day) to read the information sheet, think about participation, and discuss it with their family members. The researchers will acquire participants’ written informed consent on the next day.

The recruitment period is expected to extend over a 3‐month period. Data will be collected before randomization (baseline), immediately after the intervention (post‐test 1), and 3 months after the intervention (post‐test 2). Recruitment of participants began in May 2020. Primary endpoints (baseline and post‐test 1) and follow‐up measure (post‐test 2) will be expected to be completed in January 2021.

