#### Data analysis

3.2.8

Data will be analysed using the Statistical Package for Social Sciences (SPSS). An intention‐to‐treat analysis (ITT) will be adopted to manage missing data. Descriptive statistics were conducted to describe the sociodemographic and clinical characteristics of primiparous women by means and standard deviations (SDs); frequencies and proportions. The chi‐square (χ2) and the independent sample *t* test will be used to detect any significant difference between the study and control groups on the baseline variables. Adjusted for possible confounding factors of sociodemographic variables, the repeated measures triply MANCOVA will be conducted to determine whether the intervention of ISP is effective in enhancing *MSE* and social support and for reducing PPD across the three time points of data collection (baseline, post‐test 1, and post‐test 2). The independent *t* test will be used to compare how satisfied the intervention group and the control group are with the health care that they received after childbirth on the two time points of immediately after the intervention and 12 weeks after intervention.

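### Pre-randomization baseline scores serve as a response occasion, not a covariate, and the hypothesis lists baseline as a time of expected arm difference; baseline adjustment would gain precision at no cost

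*Protocol article*

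**What the plan says.** - **Timing of baseline** (Recruitment, 3.2.3): "Data will be collected before randomization (baseline"). The same section counts baseline and post-test 1 together as primary endpoints and calls post-test 2 the follow-up measure.
- **Hypothesis** (Aim, 3.1): "compared with the control group at baseline, post‐test 1, and post‐test 2, women in the intervention group will report statistically significant" benefits in self-efficacy, social support, depressive symptoms and satisfaction. Under the Data collection procedure (3.2.7), satisfaction is collected only at the two post-tests.
- **Efficacy model** (Data analysis, 3.2.8): one multivariate repeated-measures analysis of the three scales "across the three time points of data collection (baseline, post‐test 1, and post‐test 2"). The only covariates named are sociodemographic. Baseline variables are also compared between arms by chi-square and t tests.
- **Sample size** (Study setting and participants, 3.2.2): "With a power of 0.80, an alpha set at 0.05, and an effect size of 0.35 for the primary outcome of PPD (EPDS scores"), from which "each group will be 90 women" before attrition.

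The article does not say whether the group main effect or the group-by-time interaction decides efficacy.

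**The concern.** A score taken before randomization cannot be affected by the intervention. Its expected arm difference is zero, so it says nothing about the effect as a response. Its value lies in explaining between-woman variation in the later scores, which is what a covariate does. The plan puts it on the response side and names no baseline score as a covariate.

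The cost depends on the deciding term. A main effect over three occasions mixes a known zero into the estimate. A group-by-time test compares changes from baseline, which carries the full baseline variance into the comparison instead of removing the part that baseline predicts. In both cases the trial gives up precision that data already collected would supply. Neither term is itself the baseline-adjusted arm difference after the intervention, which is the quantity a reader will want.

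The hypothesis repeats the framing: as written, one of its three time points is a prediction that randomization rules out in expectation.

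**Working it through.** **Inputs from the article:** standardised effect d = 0.35 on the EPDS, n = 90 per arm, alpha 0.05, 1:1 allocation, baseline before randomization.

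**Assumptions (not in the article):** two-sided test; SD 1 at each occasion; equal correlation r between any two occasions (compound symmetry), shown for 0.3, 0.5, 0.7 and 0.8; effect 0 at baseline and 0.35 at both post-tests. The degree of freedom spent on the covariate is ignored.

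**The plan's own figure first.** Attrition: 90/0.70 = 128.6, so 129 per arm and 258 in total, as stated. The 90 itself does not reproduce for an unadjusted two-sided comparison: 2(1.960 + 0.842)²/0.35² = 128.2, so 129 per arm, and 90 per arm gives about 65% power. That is a separate point; 90 is used here only as the planned number of completers.

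**Formulas.** With n/2 = 45, √45 = 6.708 and n·d² = 90 × 0.1225 = 11.025:

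1. Group main effect over three occasions. Averaged effect (0 + 0.35 + 0.35)/3 = 0.233; SD √((1+2r)/3). Noncentrality 6.708 × 0.233/√((1+2r)/3); at r = 0.5 this is 1.917 (t, 178 df).
2. Group-by-time, 2 df (Hotelling T² on the two changes from baseline). λ = n·d²/[3(1−r)]; at r = 0.5, 11.025/1.5 = 7.35 (F, 2 and 177 df).
3. Both post-tests adjusted for baseline, 2 df. λ = n·d²/[(1−r)(1+2r)]; at r = 0.5, 11.025/1.0 = 11.025.
4. Post-test 1 alone, adjusted for baseline. 6.708 × 0.35/√(1−r²); at r = 0.5, 2.711.
5. Mean of the two post-tests, adjusted for baseline. 6.708 × 0.35/√((1+r)/2 − r²); at r = 0.5, 3.320.

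**Power, EPDS alone, 90 per arm**

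| Test | r = 0.3 | r = 0.5 | r = 0.7 | r = 0.8 |
|---|---|---|---|---|
| 1. Main effect, three occasions | 56.8% | 47.9% | 41.3% | 38.7% |
| 2. Group-by-time, 2 df | 51.7% | 67.0% | 88.4% | 97.5% |
| 3. Baseline-adjusted, 2 df | 80.2% | 84.7% | 94.5% | 98.8% |
| 4. Baseline-adjusted post-test 1 | 68.7% | 76.9% | 90.5% | 97.3% |
| 5. Baseline-adjusted mean of post-tests | 87.7% | 91.0% | 97.3% | 99.6% |

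Rows 2 and 3 are the like-for-like comparison, with the same post-tests and the same degrees of freedom. The ratio of their noncentralities is 3/(1+2r): 1.88, 1.50, 1.25 and 1.15 at the four correlations. It exceeds 1 for every r below 1 and approaches 1 as r rises.

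**Effect at post-test 1 only** (r = 0.3/0.5/0.7). Group-by-time is unchanged at 51.7/67.0/88.4%. The adjusted 2-df test has 60.6/72.5/90.3%, adjusted post-test 1 has 68.7/76.9/90.5%, and the three-occasion main effect has 18.7/15.9/14.0%.

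**All three scales jointly**, each moving by 0.35, with an assumed between-scale correlation of 0.3 (r = 0.3/0.5/0.7). Group-by-time 61.7/78.8/96.2%, main effect 67.9/57.2/48.9%, baseline-adjusted 6-df test 90.7/93.9/98.9%. The ordering is the same as for the EPDS alone.

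**The case against.** The strongest reply is that a repeated-measures analysis including baseline is a recognised choice, and that in a pre-test and repeated post-test design the natural test is group-by-time, where baseline is the reference and nothing is averaged down. This largely stands. A reader might infer that the plan dilutes the effect to two thirds. The article does not support that as a flat statement, because it never names the main effect as the deciding term. Nor does group-by-time bias the result: regression to the mean acts on both arms alike in expectation, and nothing here shows an inflated type I error. Under that reading the loss is one of precision.

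Second, the size of the loss rests on a correlation the article does not give. At 0.8, group-by-time (97.5%) and adjusted post-test 1 (97.3%) are level. It would also be wrong to credit the recommended post-test 1 contrast with 87.7% to 91.0% power at correlations of 0.3 and 0.5. Those figures belong to the mean of the post-tests; post-test 1 alone has 68.7% to 76.9%.

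Third, the reference to baseline in the Aim may be loose drafting that lists the assessment times. The Data analysis section treats baseline arm differences as a comparability check and tests satisfaction only at the post-tests. The wording is therefore not evidence that a treatment effect at baseline will be tested, but as a stated hypothesis it still needs correcting.

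Finally, the deciding term may be set out in a fuller plan, and its absence from the article is not the complaint. The response occasions and the type of covariate are stated in the article, and on those terms either candidate test has less power than its baseline-adjusted counterpart.

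**Conclusion.** The point holds as an avoidable loss of precision and a hypothesis that needs rewording, not as a bias or an invalid test. It should be fixed as a free improvement.

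Under group-by-time, the matched baseline-adjusted test gains 28.5, 17.7 and 6.1 percentage points of EPDS power at correlations of 0.3, 0.5 and 0.7, and 1.3 points at 0.8. Against the recommended post-test 1 contrast alone, the gain is 17.0, 9.9 and 2.1 points, and nil at 0.8. Under the main-effect reading, the estimate itself shrinks from 0.35 to 0.233 and power falls to between 56.8% and 41.3% over correlations of 0.3 to 0.7.

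These sizes assume 90 completers per arm, a two-sided 5% test, compound symmetry and an effect of 0.35 at both post-tests. In the matched comparisons shown, the direction does not depend on the correlation; the size does.

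**What to change.** 1. In the Aim, remove baseline from the times at which an arm difference is expected, leaving post-tests 1 and 2.
2. In Data analysis, take post-tests 1 and 2 as the responses and include the baseline score of the same scale as a covariate. A constrained longitudinal model with a common baseline mean in both arms is an equivalent alternative. The sociodemographic covariates can stay.
3. Name the adjusted arm difference at post-test 1 as the deciding contrast and report it with a 95% confidence interval. This fits the Recruitment section, which places post-test 1 with the primary endpoints and treats post-test 2 as follow-up. Baseline should no longer be described there as an endpoint.

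The cost is a few sentences in the Aim, Recruitment and Data analysis sections. The baseline scores are already collected from every participant, so no additional data or visits are needed.

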#### Data collection procedure

3.2.7

The baseline assessment will be conducted by the researchers and every participant will be asked to complete the SICS, EPDS, PSSS, and social‐demographic and clinical data in the obstetric wards. Post‐test 1 will be carried out immediately after the intervention and Post‐test 2 will be conducted on 3 months after the intervention. At the two time points of Post‐tests 1 and 2, the questionnaires comprised of SICS, EPDS, PSSS, and healthcare satisfaction will be sent to participants by wechat or email; and the completed questionnaires will be returned to the researchers by wechat or email. To improve the response rate, a kindly telephone or wechat reminder will be given to participants before and after one week of the two time points, respectively.

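### The two unadjusted t tests for satisfaction are valid under randomisation, but they forgo a possible modest gain in precision and leave arm-differential non-return uncorrected

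*Protocol article*

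**What the plan says.** All places are in the protocol article.

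- **Aim:** the third hypothesis is "Great satisfaction with healthcare received after childbirth". Outcome measurements lists satisfaction as the secondary outcome, measured by three items written by the researcher. Of the three items shown, one asks for an overall rating and two ask for free text.
- **Data analysis, satisfaction:** an independent t test "will be used to compare how satisfied the intervention group and the control group are with the health care that they received", "on the two time points of immediately after the intervention and 12 weeks after intervention". No covariate is named, and nothing links a woman's two ratings.
- **Data analysis, other outcomes:** "Adjusted for possible confounding factors of sociodemographic variables, the repeated measures triply MANCOVA will be conducted" for maternal self-efficacy, social support and depression over three time points.
- **Data collection procedure:** at baseline, "every participant will be asked to complete the SICS, EPDS, PSSS, and social‐demographic and clinical data in the obstetric wards". Satisfaction is collected only at the two post-tests, on forms sent and returned by WeChat or email. Participants get reminders around each post-test, with no distinction by arm.
- **Intervention and its Table 1:** the intervention arm alone also gets a weekly telephone reminder to log in, and the program's fifth module includes a prompt to fill in questionnaires.
- **Study setting and participants:** 30% attrition is planned for. Data analysis names intention-to-treat as the way to handle missing data and gives no method.

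**The concern.** Satisfaction is the only hypothesised outcome whose stated analysis uses neither covariates nor the repeated measurement. It has no value before randomisation, so the other baseline variables are the only pre-randomisation information that could sharpen the comparison.

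Two things are at stake. First, if those variables predict satisfaction, an adjusted comparison of the same women has a smaller standard error. Second, a t test uses only the forms that come back. If return depends on, say, baseline mood, and does so differently in the two arms, the returners are no longer balanced on mood and the raw difference moves. A model that includes the baseline score corrects that part of the shift.

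This is a method that the article states, not a detail left to a fuller document.

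**Working it through.** **Inputs.** From the article: 129 women per arm, 30% attrition, alpha 0.05, effect size 0.35 (given for EPDS, borrowed here only as an illustration). Returners per arm: 129 × 0.70 ≈ 90. The article's attrition step agrees: 90 / 0.70 = 128.6, rounded up to 129. It gives no figure for satisfaction, so there is none to reproduce. The R² between baseline data and satisfaction, and all return patterns below, are assumptions.

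**1. Precision.** The unadjusted standard error, in SD units, is √(2/90) = 0.149. With p covariate parameters and 180 returners, the variance of the adjusted difference relative to the unadjusted one is about (1 − R²) × 177/(177 − p). The second factor is the cost of estimating the covariates. It is ignored in the first results column; p = 10 stands for a long set with several categorical variables and p = 5 for a short one.

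| R² | √(1 − R²), cost ignored | p = 5: factor 177/172 = 1.029 | p = 10: factor 177/167 = 1.060 |
|---|---|---|---|
| 0.05 | 0.975 | √0.978 = 0.989 | √1.007 = 1.003 |
| 0.10 | 0.949 | √0.926 = 0.962 | √0.954 = 0.977 |
| 0.20 | 0.894 | √0.823 = 0.907 | √0.848 = 0.921 |

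The standard error therefore changes by anything from no reduction (R² 0.05, p = 10) to about 9% lower (R² 0.20, p = 5), or 10.6% lower if the covariate cost is ignored.

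**2. Power, as illustration.** For a difference of 0.35 SD with 90 returners per arm, two-sided 0.05, normal approximation and covariate cost ignored, power is 65.1% unadjusted. It is 67.3%, 69.7% and 74.7% at R² of 0.05, 0.10 and 0.20. (That 65% falls short of the article's 80% for the same inputs is a separate matter about the sample size.)

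**3. Non-return.** Simulation with 2,000,000 women per arm and no true effect. A baseline score X has correlation ρ with satisfaction, and the log-odds of non-return change by a given slope per SD of X. Entries are the absolute raw difference among returners, in SD.

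| Slope, intervention / control | Non-return, intervention / control | ρ = 0.20 | ρ = 0.30 | ρ = 0.45 |
|---|---|---|---|---|
| 0.5 / 0.5 | 30% / 30% | 0.001 | 0.000 | 0.001 |
| 0.5 / 0.5 | 30% / 9% | 0.021 | 0.030 | 0.045 |
| 0.5 / 0 | 30% / 30% | 0.028 | 0.045 | 0.067 |
| 1.0 / 0 | 30% / 30% | 0.051 | 0.076 | 0.113 |
| 0.5 / −0.5 | 30% / 30% | 0.057 | 0.088 | 0.129 |

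Adjusting for X leaves 0.002 SD or less in every row. That is built in, because return here depends on X alone. The largest raw shift, 0.129 SD, is 0.129/0.149 = 0.87 of one unadjusted standard error and 37% of a 0.35 SD effect. The smallest non-zero pattern, 0.021 SD, is 6% of it.

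**The case against.** The strongest reply is that nothing here is an error. Under 1:1 randomisation an unadjusted t test at each post-test is a valid comparison, and that the same women answer twice does not invalidate either test. The outcome is secondary and appears to rest on about one rating. With a weak R² and many covariates there is no gain at all. All of this stands and limits the weight of the point.

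A reader might infer more than the documents support:

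- *That the t test is biased.* It is biased only if return, or its dependence on baseline, differs by arm. The weekly calls and the in-program prompt make that plausible, but nothing shows that it will happen, and both arms get reminders around the post-tests.
- *That the adjusted model is free of bias.* It corrects only what the included variables explain. If return depends on satisfaction itself beyond those variables, the adjusted estimate is shifted too.
- *That precision is certainly lost.* The article gives no R².
- *That the article breaks its own rule.* The main model is adjusted for sociodemographic variables only. Baseline EPDS and PSSS enter it as repeated outcomes, not covariates, so using them for satisfaction goes beyond consistency with that model.

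It can also be said that missing-data detail belongs in a fuller plan. That is fair for the general intention-to-treat statement. But the satisfaction method is fixed in the text, and intention-to-treat, which names no imputation or model, does not change what a t test on returned forms does.

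**Conclusion.** The point holds as a modest, low-cost improvement to a stated analysis of a secondary outcome. It is not a claim that the planned t tests are wrong. The precision forgone is about 0 to 10% of the standard error, on an assumed R² of 0.05 to 0.20 and depending on the number of covariates. The exposure to non-return is about 0.02 to 0.13 SD, on an assumed correlation of 0.20 to 0.45 between a baseline score and satisfaction and on the differential return patterns tabulated; it is about 0 if return is the same in both arms. Neither R² nor the return pattern can be read from the article.

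**What to change.** Make the main analysis of the satisfaction rating one linear mixed model over both post-tests, with arm, time, arm-by-time and a short prespecified covariate set: baseline EPDS, baseline PSSS and a few sociodemographic variables. Report the adjusted arm difference at each post-test, and keep the raw means and t tests as description. A woman who returns only one form then still contributes to a single analysis.

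The article does not list which sociodemographic variables the main model will use, so they must be named, and named before unblinding; choosing them afterwards would invite selective reporting. Keep the set short, because the working shows that a long one can cancel the gain.

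The cost is a sentence or two in the analysis section and a standard SPSS mixed-model procedure, with no new data. The downside is a few degrees of freedom and reliance on data being missing at random given the included variables. State that assumption alongside the result.

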### Ethical considerations

3.3

Research ethical committee approval is obtained by the Research Ethics Committee of Health Science Center in a University of China (approval number 2,020,011). The registration number with the Chinese Clinical Trial Registry is ChiCTR2000033154. This study will adhere to ethical standards for the whole procedure. There is no potential risk or harm by participating in this program. Women will not be deprived of any treatment and routine care. The written informed consent will be obtained from every participant before data collection. Women will be informed of freedom to withdraw at any time and are assured of anonymity by using special code numbers to identify themselves. All of the collected data will be kept anonymously and confidentially.

### Validity and reliability

3.4

This study adopts the rigorous research design, such as the sound theoretical framework, a RCT design with a good representative and predetermined sample, the use of instruments with a high validity and reliability, and statistically scientific analysis, which can be seen to reduce bias effectively and enhance the generalizability of research results beyond the target population. Moreover, outcome assessors and data analysts of the research will be blinded after assignment to interventions to reduce the biases in evaluation of the effects of the intervention.

## DISCUSSION

4

To my knowledge, this study will be the first RCT by internet on parenting outcomes for Chinese primiparous women. If the ISP program has positive outcomes, it will contribute to the scientific and practical knowledge of nursing interventions to support primiparous women on parenting outcomes; and could become the routine health care for health professionals to enhance parenting ability and mental well‐being of new mothers.

### Limitations

4.1

Some limitations need to be noted in the research. First, due to the nature of the research, blinding of researchers during all the research process is not possible and it may lead to the potential biases. Secondly, the participants are limited to those who are willing to participate in this study via internet. The results might not be generalized to those who refused to participate in the research or those who are not available to the internet. Thirdly, the longer‐term intervention will be conducted in this study and some participants may be loss during the follow‐up that can decrease the study power. To overcome the problems, a 30% attrition rate is considered in the sample size calculation and an ITT analysis will be performed in the research.

